## Abstract

**Background:**

Informal caregivers (ie, individuals who provide assistance to a known person with health or functional needs, often unpaid) experience high levels of stress. Caregiver stress is associated with negative outcomes for both caregivers and care recipients. Mindfulness-based interventions (MBIs) show promise for improving stress, emotional distress, and sleep disturbance in caregivers of persons with Alzheimer disease and related dementias (ADRD). Commercially available mobile mindfulness apps can deliver MBIs to caregivers of persons with ADRD in a feasible and cost-effective manner.

**Objective:**

We are conducting a single-blind feasibility proof-of-concept randomized controlled trial (RCT; National Institutes of Health [NIH] stage 1B) comparing 2 free mobile apps: the active intervention Healthy Minds Program (HMP) with within-app text tailored for addressing stress among caregivers of persons with ADRD, versus Wellness App (WA), a time- and dose-matched educational control also tailored for caregivers of persons with ADRD.

**Methods:**

We aim to recruit 80 geographically diverse and stressed caregivers of persons with ADRD. Interested caregivers use a link or QR code on a recruitment flyer to complete a web-based eligibility screener. Research assistants conduct enrollment phone calls, during which participants provide informed consent digitally. After participants complete baseline surveys, we randomize them to the mindfulness-based intervention (HMP) or educational control podcast app (WA) and instruct them to listen to prescribed content for 10 minutes per day (70 minutes per week) for 12 weeks. Caregivers are blinded to intervention versus control. The study team checks adherence weekly and contacts participants to promote adherence as needed. Participants complete web-based self-report measures at baseline, posttest, and follow-up; weekly process measures are also completed. Primary outcomes are a priori set feasibility benchmarks. Secondary outcomes are stress, emotional distress, sleep disturbance, caregiver burden, mindfulness, awareness, connection, insight, and purpose. We will calculate 1-sided 95% CI to assess feasibility benchmarks. Effect sizes of change in outcomes will be used to examine the proof of concept.

**Results:**

Recruitment started on February 20, 2023. We have enrolled 27 caregivers (HMP: n=14; WA: n=13) as of June 2023. Funding began in August 2022, and we plan to finish enrollment by December 2023. Data analysis is expected to begin in May 2024 when all follow-ups are complete; publication of findings will follow.

**Conclusions:**

Through this trial, we aim to establish feasibility benchmarks for HMP and WA, as well as establish a proof of concept that HMP improves stress (primary quantitative outcome), emotional distress, sleep, and mindfulness more than WA. Results will inform a future efficacy trial (NIH stage II). HMP has the potential to be a cost-effective solution to reduce stress in caregivers of persons with ADRD, benefiting caregiver health and quality of care as well as patient care.

**Trial Registration:**

ClinicalTrials.gov NCT05732038; https://clinicaltrials.gov/study/NCT05732038

**International Registered Report Identifier (IRRID):**

DERR1-10.2196/50108

## Introduction

### Background

More than 1 in 5 Americans (ie, approximately 53 million) are informal caregivers [1]. These individuals provide assistance to known persons with physical, mental, or cognitive illness or disability, often unpaid [2]. Almost half of caregivers who provide help to older adults care for someone with Alzheimer disease or related dementias (ADRD) [3]. Caregivers have been dubbed “the hidden patients” because the negative physical and mental health consequences of caregiving are often underrecognized and undertreated [4]. Nearly 60% of caregivers of persons with ADRD experience high levels of psychological stress, and more than 1 in 3 caregivers of persons with ADRD report that their health has deteriorated due to caregiving responsibilities [5]. Some key sources of caregiver stress include ongoing worry about their loved one’s health, concerns about whether they are doing the caregiving job well, challenges navigating regular life in addition to caregiving responsibilities, concerns about the impact of caregiving on their own health, social isolation, and financial strain [6,7]. High caregiver stress is associated with mental health concerns [8], sleep difficulties [9], and an increased risk for morbidity and mortality [10]. In previous studies, 42%-55% of caregivers reported looking for feasible and effective stress management interventions [11]; yet this population often has limited time for outpatient psychotherapy. Given the negative consequences of caregiver stress on the health and well-being of both caregivers and care recipients, decreasing caregiver stress in an accessible delivery format is a public health concern.

Mindfulness-based interventions (MBIs) show promise as an efficacious nonpharmacological treatment to reduce caregiver stress [2]. Mindfulness meditation is defined as paying attention on purpose, in the present moment, nonjudgmentally [12,13]. Practicing mindfulness is thought to help individuals cultivate acceptance and inner peace, regardless of challenging life circumstances [14-16]. Across many populations, the practice of mindfulness meditation is associated with decreased stress [17,18], improved emotional functioning [19,20], and improved sleep [21,22]. Several recent systematic reviews have supported the effectiveness of MBIs for improving stress, emotional functioning, and sleep in caregivers, including caregivers of persons with ADRD [2,14,17,18,21,23-27].

Although research has established the benefits of MBIs for caregivers, the prevailing models of delivery of these interventions fall short for several reasons. First, many of these programs are conducted in person [28], which is sometimes not feasible for caregivers’ schedules (eg, needing respite for care recipients) [7]. Second, even when programs have been delivered remotely, these often follow a synchronous format (ie, caregivers must attend remotely at the same time each week), which is challenging given the unpredictability of caregiving responsibilities. Third, traditional programs typically demand substantial amounts of continuous time that caregivers are unable to commit (eg, a traditional mindfulness-based stress reduction program involves 8 weekly 2.5- to 3.5-hour-long sessions as well as 45 minutes of prescribed practice per day) [29]. Fourth, traditional programs require trained providers who are often costly, are not usually covered by insurance, and are not always readily available [30-32]. More feasible, scalable, and cost-effective solutions are needed to deliver MBIs to caregivers.

Mobile mindfulness apps may be uniquely positioned to address the aforementioned barriers by allowing caregivers to practice meditation on their own schedule at little or no cost. The majority of caregivers own a smartphone and regularly use mobile apps [33]. Additionally, adults aged 50 years or older, who represent a sizable portion of caregivers of persons with ADRD, are the fastest-rising users of smartphone technology in the past decade [34]. In qualitative studies, caregivers express interest in using mobile apps for stress management and health information [35] including to learn mindfulness meditation for stress management [36-39]. To the best of our knowledge, there are no consumer-based mobile apps with proven efficacy in decreasing stress, emotional distress, and sleep difficulties among caregivers of persons with ADRD [40]. Although mindfulness-based mobile apps show promise for helping caregivers of persons with ADRD decrease stress, emotional distress, and sleep difficulties, additional research is needed to establish feasibility and efficacy before widespread dissemination.

Healthy Minds Program (HMP) is a mindfulness-based mobile app that may be well suited for use with caregivers of persons with ADRD for several reasons. First, HMP is unique because it teaches mindfulness skills grounded in theory [41] with empirical support [42-44]. Having a theoretical underpinning is important because it allows the app to be a vehicle for the delivery of evidence-based mindfulness skills. Second, previous research has shown that HMP reduced emotional distress and burnout in firefighters [44]; improved psychological distress, stress, social connectedness, and mindfulness in adults [43]; and reduced stress and increased mindfulness, self-compassion, and human flourishing in medical students [42]. Third, HMP is free of charge, which increases its reach especially among caregivers who often experience financial burdens because of their role. Fourth, HMP has customizable features (eg, a diverse set of voices to choose from) that have the potential to increase acceptability across race, ethnicity, and gender. Finally, HMP supports content tailoring to include on-screen language and scenarios that are relevant for caregivers of persons with ADRD.

Here, we will be conducting a National Institutes of Health (NIH) stage 1B trial (NCT05732038) comparing HMP with a time- and dose-matched educational control app, Wellness App (WA). Our team tailored the content of both apps to highlight case scenarios specific to caregivers of persons with ADRD. Both interventions (HMP and WA) consist of 12 weeks of guided listening for 10 minutes per day. Participants complete outcome measures at baseline, posttest, and follow-up (2 months after posttest), as well as weekly process measures.

### Objectives

The purpose of this paper is to describe the protocol and status of our ongoing single-blind feasibility proof-of-concept randomized controlled trial (RCT) of HMP versus WA in caregivers of persons with ADRD. Our primary hypothesis is that HMP and WA will meet a priori feasibility markers (ie, acceptance and demand benchmarks). Our secondary hypothesis is that participation in HMP will be associated with a greater decrease in caregiver stress (primary quantitative outcome), emotional distress, sleep dysfunction, and caregiver burden, and a greater increase in mindfulness, awareness, connection, insight, and purpose (secondary quantitative outcomes) compared with WA, and improvement will be sustained through the 20-week follow-up. Results will directly inform an NIH stage 2 fully powered RCT of HMP versus WA.

## Methods

### Study Design and Setting

This NIH stage 1B, single-blind, feasibility, proof-of-concept RCT is testing HMP versus WA (time- and dose-matched control) in caregivers of persons with ADRD. Data collection is underway (started in February 2023; n=27 caregivers as of June 2023). We plan to recruit 80 caregivers of persons with ADRD reporting elevated levels of stress. Our institutional review board approved this study (2022P001601). Figure 1 provides an overview of the study design and timeline.

**Figure 1 figure1:**
[figure not shown]
Study design and timeline. HMP: Healthy Minds Program; RA: research assistant; WA: Wellness App.

### Inclusion and Exclusion Criteria

Table 1 presents the study inclusion and exclusion criteria and rationale. These eligibility criteria were informed by previous MBI studies with caregivers, including those of persons with ADRD [2,14,17,18,21,23-27], as well as a previous study with caregivers funded by the NIH (NCT00177489). The criteria are meant to be as inclusive as possible to maximize generalizability by allowing individuals who self-identify as caregivers to participate rather than requiring a certain number of hours spent caregiving, specific responsibilities, or other criteria.

**Table 1 table1:** Study inclusion and exclusion criteria and rationale.

Criteria			Rationale
**Inclusion**			
	Age 18 years or older	Most caregivers are adults; study procedures are formulated for adults only	
	English fluency and literacy	Measures, instructions, and app are in English	
	Meeting criteria for being a caregiver (ie, family or friend of a care recipient who provides care not through an agency) [2]	Population	
	Perceived Stress Scale (4 items) version ≥6 [45]	Population; ensure that the intervention is needed (not all caregivers experience caregiver stress)	
	Willing to be randomized	Necessary for scientific rigor	
	Care recipient must be rated >1 on the Functional Assessment Staging Tool [46]	Population; ensure that caregivers have a threshold of caregiving tasks	

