**Acceptability benchmarks**					
	Feasibility of recruitment	We will assess the number of caregivers enrolled from the number of caregivers who were eligible		80 caregivers will be recruited in 6 months; ≥70% of eligible caregivers will enroll	
	Treatment satisfaction	We will use the Client Satisfaction Questionnaire [64] to assess caregivers’ satisfaction with the intervention		At least 70% of caregivers will have scores on the Client Satisfaction Scale over and above the midpoint in both the HMP^a^ and WA^b^ groups	
	Credibility and expectancy	We will use the Credibility and Expectancy Questionnaire [65] to assess caregivers’ perceptions that the treatment will work after learning about the study.		At least 70% of caregivers will have scores on the Credibility and Expectancy Scale above the midpoint in both the HMP and WA groups.	

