### Data Analysis

We will assess the acceptability and demand of the intervention in line with Bowen and colleagues’ standards for feasibility studies and components of the Behavioral Change Consortium’s Treatment Fidelity model [63,67]. Specifically, we will assess the acceptability, credibility, satisfaction, and perceived appropriateness and usefulness of the daily prescribed app content. Benchmarks and measurements for each feasibility construct are listed in Table 2. One-sided 95% CI will be calculated for each proportion to evaluate feasibility benchmarks. Depending on the nature of the estimate or comparison, exact binomial tests, Fisher exact tests, 2-tailed *t* tests, or correlations may be used to summarize the data and test for statistical significance. HMP and WA user data (ie, what content users listened to, when, and for how long) are collected automatically from users.

Consistent with guidelines for early feasibility studies, our analysis will not assess efficacy, as we are not powered to do so [68]. However, we will estimate between-group differences in changes from baseline to posttest (12 weeks) to follow-up (20 weeks) as proof of concept that the intervention shows promise with the intended population [63]. Variance components and effect sizes will be estimated for each outcome. We will use variance estimates from repeated-measures analysis of data on Perceived Stress Scale-10 to guide the design and power calculations for a future trial testing efficacy [69,70]. We will compute the effect sizes of change in these scores to cautiously guide future work. Proof of concept will be demonstrated if the decrease in caregiver stress (Perceived Stress Scale-10, the primary outcome in future trials) in the intervention group from baseline to posttest is greater than in the WA group, with at least small to moderate effect sizes favoring HMP (between-group test of superiority).

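### Because Table 1 makes willingness to be randomized part of eligibility, the ≥70% enrolled-over-eligible benchmark may overstate acceptance of the randomized design

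*Protocol article*

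**What the plan says.** In the protocol article, Methods, Inclusion and Exclusion Criteria, Table 1 includes "Willing to be randomized" among the inclusion criteria, with the rationale "Necessary for scientific rigor". The text introducing the table treats its entries as the eligibility criteria: "Table 1 presents the study inclusion and exclusion criteria and rationale. These eligibility criteria were informed by previous MBI studies with caregivers".

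Under Feasibility Markers, Table 2 describes recruitment feasibility as follows: "We will assess the number of caregivers enrolled from the number of caregivers who were eligible". The criterion has two parts. One is a count, 80 caregivers within 6 months. The other is a percentage: "≥70% of eligible caregivers will enroll". The Abstract gives these markers primary status: "Primary outcomes are a priori set feasibility benchmarks".

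Two further sections bear on who is counted.
- **Recruitment and Screening** describes an online questionnaire that tells ineligible caregivers so on screen. Those who pass then confirm their interest and book a call. FAST, and the SPMSQ for older caregivers, are given only on that call.
- **Enrollment** places the consent review after the caregiver has been found eligible on the call.

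The article does not say when or how willingness to be randomized is asked.

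**The concern.** A feasibility trial ahead of a larger randomized trial should show, among other things, whether the target population accepts random allocation. The natural place to see this is the uptake proportion. Here the numerator (enrolled) and the denominator (eligible) are both conditioned on acceptance of randomization, because that acceptance is one of the eligibility criteria. Anyone who meets every other criterion but declines randomization fails Table 1 and so leaves the denominator.

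No wording in the article defines eligibility differently for this benchmark, and no other marker in Table 2 counts refusals of randomization. At stake is the pass or fail result of a primary outcome, and what it can be taken to say about recruitment to the planned stage 2 trial of the same two apps.

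**Working it through.** There is no figure in the plan to reproduce, since the 70% threshold is stated without derivation. The check is therefore how the benchmark behaves under the two denominators.

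**Inputs from the article**
- Enrolled: 80, the target in Study Design and Setting ("We plan to recruit 80 caregivers of persons with ADRD reporting elevated levels of stress").
- Threshold: 70% (Table 2).
- Interval: "One-sided 95% CI will be calculated for each proportion to evaluate feasibility benchmarks" (Data Analysis).

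**Assumed inputs (the article gives neither)**
- E, the number eligible as defined in Table 1: 90 to 114.
- R, the number who meet the other criteria but decline randomization and so are left out of E: 0 to 40.

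**Formulas**
- Uptake as written = 80/E.
- Uptake with refusers counted = 80/(E + R).

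**Largest denominator that passes.** 80/0.70 = 114.3, so at most 114 caregivers. The point estimate falls below 70% once E + R reaches 115 (80/115 = 69.6%).

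**Results for E = 100.** As written, uptake is 80/100 = 80.0%, with a one-sided 95% lower limit of 72.3% (exact Clopper-Pearson, an assumed choice of method), whatever the value of R. With refusers counted:

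| R | 80/(100 + R) | Lower limit |
|---|---|---|
| 0 | 80.0% | 72.3% |
| 5 | 76.2% | 68.4% |
| 10 | 72.7% | 64.9% |
| 15 | 69.6% | 61.7% |
| 20 | 66.7% | 58.9% |
| 40 | 57.1% | 49.8% |

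The point estimate falls below 70% at R = 15, that is, when 15/115 = 13.0% of otherwise eligible caregivers decline. If the lower limit is the yardstick, it is already below 70% at R = 5.

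**Smallest R that moves the point estimate below 70%** (R = 115 − E):
- E = 90: 25
- E = 100: 15
- E = 110: 5
- E = 114: 1

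The closer the reported uptake lies to 70%, the fewer uncounted refusals are needed to change the result.

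**The case against.** The strongest reply is that the criterion is routine, that enrolled over eligible is an ordinary definition of uptake, and that a condensed article may leave the classification of screen failures to a fuller document. The first two points are true of each element taken alone. The problem lies in combining them, and the article states both. A fuller document could supply a different definition for the benchmark, but followed as written Tables 1 and 2 exclude refusers.

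A reader might go further and infer that the benchmark cannot register refusal of randomization at all, or can be passed however many refuse. The article does not support that, for two reasons.
- Under Enrollment, eligibility is settled before the consent form is reviewed. A caregiver who refuses at consent may already be logged as eligible and counted as a non-enroller. Whether this happens is not stated.
- The count of 80 in 6 months is part of the same criterion, and widespread refusal would slow accrual. That part responds only indirectly, however, and cannot separate refusals from limited reach or from the removal of suspected imposters.

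A reader might also infer that stage 2 recruitment planning will be too optimistic. That is possible but not shown. The article says the results will inform stage 2 but describes no recruitment forecast built on this proportion; the input it names for the future design is the variance of the Perceived Stress Scale-10. If stage 2 keeps the same criterion, the same ratio carries over on the same definition. Refusals may also be few, since both arms receive a free app tailored to caregivers and matched in time and dose.

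Finally, eligible caregivers who decline for other reasons still count against the benchmark, so the circularity is only partial.

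**Conclusion.** The point holds in a limited form. With Tables 1 and 2 taken as written, caregivers who decline randomization at screening fall out of the denominator of the percentage benchmark, so the uptake figure may overstate acceptance of the randomized design. The treatment of those who refuse at consent is unclear.

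The size cannot be determined from the article. The illustrated drop from 80.0% to 72.7% or 69.6% rests on assumed values of 100 eligible caregivers and 10 or 15 refusers. It shows that the pass or fail result can turn on this definition alone, not that it will. The change is worth making because the benchmark is a primary outcome and the correction is small.

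**What to change.** Keep willingness to be randomized as a condition of enrollment. In Table 2:
1. Define the uptake denominator as caregivers who meet all other criteria assessed up to the point of refusal. For those who decline online, that means the other screener criteria.
2. Count those who decline randomization at any stage, including at consent, as eligible non-enrollers.
3. Report their number separately.
4. Show uptake with and without the online refusers.

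The cost is a short addition to Table 2 and a count from the screening records, provided these hold the answer on randomization. At the time of the article 27 of 80 caregivers had been enrolled, so refusals could still be recorded prospectively for the rest.

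There are two drawbacks. The uptake figure may look less favourable. It will also be slightly conservative, because online refusers have no FAST or SPMSQ result and some may have proved ineligible on the call; presenting both versions deals with this.

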**Exclusion**			
	Any planned change in psychotropic pharmacologic treatment for the duration of the study	Treatment confound	
	Use of any consumer-based mindfulness meditation app for more than 60 minutes per month in the past 6 months	Treatment confound	
	Current participation in a meditation program (eg, mindfulness-based stress reduction, mindfulness-based cognitive therapy, etc)	Treatment confound	
	Major illness anticipated to worsen dramatically or require surgery in the next 20 weeks (study duration)	Treatment confound	
	Active treatment for cancer (chemotherapy or radiation)	Treatment confound	
	Imminent placement of care recipient in a nursing home or with another caregiver (within 4 months)	Treatment confound	
	Involvement in another clinical trial for caregivers	Treatment confound	
	For participants aged 65 years and older: Short Portable Mental Status Questionnaire: ≥4 errors [47]	Validity and feasibility	

